## Analysis

### Baseline Analyses

To assess external validity, demographic, and clinical characteristics of study participants', responses at baseline will be compared for participants who are subsequently randomised and participants who are screened but not randomised. The specific criteria by which participants are excluded from randomisation will be tabulated. Demographic and clinical characteristics will be compared between CAAT-PARK and TAU groups to identify potential imbalances not accounted for by randomisation.

### Efficacy Analysis of Primary Outcomes

The efficacy of CAAT-PARK will be determined by comparing the mean change in values of the two groups from baseline to week 12 follow-up. Analysis between the two groups will be made using an independent sample *t*-test. Intention to treat (ITT) and per protocol (PP) analyses will be undertaken. For the intervention group, this is irrespective of their compliance with CAAT-PARK. ITT analysis will represent the primary analysis and will be used for evaluation of all outcomes. PP analysis will include patients who comply with the treatment as defined by completing five or more out of seven CAAT-PARK sessions. All participants will undergo sub-group analysis testing for potential effect modification for the presence of a spouse/carer on the treatment effect. Appropriate adjustments will be made in the statistical analyses for potential factors that are unevenly distributed between the groups. Specifically, participants with significantly high reported levels of cognitive impairment and anxiety and depression at baseline (assessed with the MoCA and HADS, respectively) will be analysed to determine the independent impact of these prognostic factors on the treatment effect. Adjusted estimates will be obtained by identifying baseline imbalances and incorporating these into a regression model using pre and post intervention primary outcome scores.

If normal distribution assumptions are not met, even after suitable transformations, non-parametric analysis will be adopted. Imputation for missing/incomplete data will be carried out using chained equations with all outcome measures and potentially correlated baseline values. A total of 10 imputed datasets will be created.

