**Methods/Design:**

A parallel, randomised controlled trial will be conducted to investigate whether carer assisted adherence therapy is effective for improving medication adherence and quality of life. We aim to recruit 40 patient/carer pairs into each group. Participants will be randomly assigned by the Clinical Research Trials Unit at the University of East Anglia. Adherence therapy is a brief cognitive-behavioural approach aimed at facilitating a process of shared decision making. The central theory is that when patients make shared choices with a professional they are more likely to continue with those choices because they are personally owned and meaningful. Outcomes will be rates of adherence and quality of life, determined by the Morisky Medication Adherence Scale-4 and the Parkinson's disease Questionnaire-39 respectively. Assessments will take place post randomisation, immediately post intervention and 12-weeks post randomisation. Primary outcomes are adherence and quality of life at 12-week follow-up. Efficacy will be determined using intention-to-treat analysis. Independent samples t-tests will compare mean changes between groups from baseline to follow-up. Per protocol analysis will be conducted based on individuals with no major protocol deviation. Where imbalances in baseline characteristics are identified, an adjusted analysis will be performed using a regression model. Analysis will be masked to treatment allocation.

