**Figure 3 F3:**
[figure not shown]
**CAAT-PARK model**.

Participants allocated to CAAT-PARK will receive seven 30 minute sessions at weekly intervals. Assessment and problem solving will be delivered twice, making up seven sessions in total. Each weekly session will incorporate a separate theme, however, each session will be participant centred. Where a patient's carer has consented to the trial, the intervention will be delivered to the carer at the same time. Ten sessions over the course of the trial will be recorded to determine treatment fidelity against the CAAT-PARK manual [49].

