### Treatment as Usual

Participants randomised to TAU will receive no additional information regarding medication adherence. Care will continue as usual according to routine practice. We will not provide any guidance to the clinical team as to the content of the usual care. Routinely usual care constitutes a clinic visit every 9-12 months to see the hospital consultant who is managing the patient's PD. Neurology specialist nurses may also see patients for routine follow-up between consultant clinics.

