### Prognostic Factors

Data from studies have shown cognitive function and mood to influence medication adherence [56,57]. It has been previously reported that depressed patients are considerably more likely to adhere poorly to medication regimens than non-depressed patients [58]. Depression has also been shown to negatively affect adherence rates in PD [23,34]. Cognitive impairment represents a major risk factor for non-adherence in people with PD [14,59]. Cognitive impairment has further been associated with under and over-use of medication in PD [14,45,57]. Therefore, it is possible that both cognitive impairment and the presence of anxiety and depression may deleteriously influence the effective uptake of the adherence intervention. We therefore aim to assess for these prognostic factors at baseline. Data collected for participants with identified cognitive impairment (assessed using the MoCA) or anxiety and depression (assessed using the HADS) will be appropriately adjusted using regression modelling. Where cognitive impairment and anxiety and depression are present in study participants at baseline assessment, analyses will be undertaken to assess their independent impact on the efficacy of CAAT-PARK. Further, we will examine which aspects of the MoCA, if any, predict poor medication adherence in the trial participants.

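### The per-protocol set has two unlinked definitions, and its session rule can select patients in the CAAT-PARK arm only; the primary ITT result is unaffected

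*Protocol article*

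**What the plan says.** The per-protocol (PP) analysis is described twice in the protocol article.

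- Abstract, Methods/Design: "Per protocol analysis will be conducted based on individuals with no major protocol deviation".
- Efficacy Analysis of Primary Outcomes: "PP analysis will include patients who comply with the treatment as defined by completing five or more out of seven CAAT-PARK sessions".

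The second section also contains a sentence placed directly after ITT and PP have both been named: "For the intervention group, this is irrespective of their compliance with CAAT-PARK". On the status of the two analyses it is clear: "ITT analysis will represent the primary analysis and will be used for evaluation of all outcomes".

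Sessions belong to one arm. The Intervention section says "Participants allocated to CAAT-PARK will receive seven 30 minute sessions at weekly intervals", and Treatment as Usual says "Participants randomised to TAU will receive no additional information regarding medication adherence".

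The discussion of Prognostic Factors bears on who is likely to attend. It says "it is possible that both cognitive impairment and the presence of anxiety and depression may deleteriously influence the effective uptake of the adherence intervention", and separately that "Cognitive impairment represents a major risk factor for non-adherence in people with PD".

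**The concern.** There are two problems.

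First, the same analysis has two definitions that pick different patients. A major-deviation rule could apply to either arm and could exclude people for reasons unrelated to attendance. A session count concerns attendance alone. The article does not say that one is a case of the other and does not define a major deviation. If the choice is left open until the data are seen, so is the PP result.

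Second, the session rule acts after randomisation and can act only on CAAT-PARK patients. Those retained have shown that they keep to a weekly programme; no matching test is set for TAU. In a trial of adherence, the kind of patient who completes the programme may also be the kind who would have improved anyway. At stake is how a PP result more favourable than ITT would be read: it could be taken as the effect in those who actually received the therapy, when part or all of it may be selection.

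**Working it through.** **Side-by-side reading**

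| | Abstract | Efficacy Analysis of Primary Outcomes |
|---|---|---|
| Basis of PP set | no major protocol deviation | at least 5 of 7 CAAT-PARK sessions |
| Can be applied in CAAT-PARK | yes | yes |
| Can be applied in TAU | yes, once defined | no, because TAU has no sessions |
| TAU criterion stated | no | no |

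The sentence that sets compliance aside fits ITT only. It cannot describe a PP set that is defined by compliance.

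**Size of the possible selection effect**

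The plan gives no figure for this, so there is none to reproduce.

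Inputs from the article (Sample Size): 40 analysed per group, alpha 0.05 (taken as two-sided; sidedness is not stated), PDQ-39 SD 8.89, target difference 6.13 points.

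Assumptions, not in the article:
- f, the share of CAAT-PARK patients who meet the threshold: 0.9 to 0.6.
- ρ, the correlation between attendance and improvement: −0.3 to 0.5.
- No true treatment effect; all 40 TAU patients kept; attendance and improvement jointly normal.

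Formulas, with c = z(1−f) and m = φ(c)/f:
- Bias in SD units: b = ρ·m.
- Standard error: √(v/(40f) + 1/40), with v = 1 − ρ²·m·(m − c).
- Chance of a result falsely favouring CAAT-PARK: 1 − Φ(1.96 − b/SE); nominal 0.025.

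Worked case, f = 0.8 and ρ = 0.3: c = −0.842; m = 0.280/0.8 = 0.350; b = 0.3 × 0.350 = 0.105 SD. On PDQ-39 this is 0.105 × 8.89 = 0.93 points, or 0.93/6.13 = 15% of the target. v = 1 − 0.09 × 0.350 × 1.192 = 0.962; SE = √(0.962/32 + 1/40) = 0.235; chance = 1 − Φ(1.96 − 0.447) = 0.065.

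Bias in SD, with the chance of a falsely favourable result in brackets:

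| f | ρ = −0.3 | ρ = 0 | ρ = 0.1 | ρ = 0.3 | ρ = 0.5 |
|---|---|---|---|---|---|
| 0.9 | −0.058 (0.013) | 0 (0.025) | 0.019 (0.030) | 0.058 (0.044) | 0.097 (0.063) |
| 0.8 | −0.105 (0.008) | 0 (0.025) | 0.035 (0.035) | 0.105 (0.065) | 0.175 (0.115) |
| 0.7 | −0.149 (0.005) | 0 (0.025) | 0.050 (0.039) | 0.149 (0.089) | 0.248 (0.181) |
| 0.6 | −0.193 (0.003) | 0 (0.025) | 0.064 (0.044) | 0.193 (0.115) | 0.322 (0.257) |

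For positive ρ the range is 0.02 to 0.32 SD. In PDQ-39 points that is 0.17 to 2.86, or 3% to 47% of 6.13. The article gives no SD for MMAS-4, so the same bias cannot be put in MMAS-4 points.

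**The randomisation-based alternative**

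TAU patients receive no sessions, so the complier-average effect is the ITT difference divided by f. With no effect of assignment on anyone, the ITT difference centres on zero, and so does this estimate, whatever ρ is.

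It assumes that assignment does nothing for patients below five sessions. If they gain an average benefit d, the estimate is shifted by d × (1 − f)/f: 0.25d at f = 0.8 and 0.67d at f = 0.6.

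Its standard error is roughly the ITT one divided by f: √(2/40) = 0.224 SD becomes about 0.224/0.8 = 0.280 SD at f = 0.8.

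**The case against.** The strongest reply is that little depends on this analysis. ITT is primary, it serves all outcomes, and no conclusion is said to rest on PP. That stands, and it limits the weight of the point.

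The two wordings can also be reconciled: attending fewer than five sessions is a natural major deviation, and detailed PP criteria are often left to a fuller document. This stands in part. The article does not make that link, and what it does fix is a rule that can select in one arm only.

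A reader might go further and infer that the session rule deletes the control arm, or that TAU enters the PP set wholly unselected. The documents support neither. The first is a literal reading that cannot have been meant. The second fills a gap, since no TAU rule is stated; under the abstract's wording, TAU patients with major deviations would drop out too.

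A reader might also infer that PP is shown to favour CAAT-PARK. It is not. The outcome is change from baseline, which removes much of any stable difference in adherence, and everyone enters with an MMAS-4 score of at least 2. Therapy is given at home, and missed sessions may reflect illness or absence rather than poor medication-taking. The bias therefore needs attendance to be related to improvement, for which the article gives no value. The mechanism is also less direct for PDQ-39 than for MMAS-4. Planned regression adjustment covers cognition and mood, which may reduce part of the bias, but it cannot deal with unmeasured reasons for attending.

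**Conclusion.** The concern holds for the secondary PP analysis. Its two definitions are not linked, the session rule applies to CAAT-PARK alone, and no TAU criterion is given, so the contrast compares a group selected after randomisation with one that has no matching filter.

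Bias towards CAAT-PARK is plausible on the article's own account, because cognition and mood are tied to both uptake and adherence. Its direction and size are not established. The range of 0.02 to 0.32 SD rests on assumed attendance of 60% to 90%, assumed correlations of 0.1 to 0.5 and a TAU group kept whole; with no correlation there is no bias, and with a negative one it reverses.

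It would be wrong to conclude that the trial's main result is compromised: the primary ITT comparison and the sample size are unaffected. This is a correctable flaw that should be settled before the PP result is produced.

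**What to change.** 1. Give one PP definition, the same in the abstract and the analysis section, with deviation criteria that can be applied to both arms.
2. Restrict the sentence that disregards compliance to the ITT analysis.
3. For the effect of receiving therapy, use a complier-average (instrumental-variable) analysis: randomised arm as instrument, at least five of seven sessions as receipt, and the same outcome and any covariates as the ITT analysis. The planned ITT comparison is a t-test with adjustment only where imbalance is found, so no further covariates are implied.
4. State the assumption that assignment has no effect below the threshold. Because one to four sessions may bring some benefit, add a sensitivity analysis that takes any session, or the number of sessions, as receipt.
5. If the attender comparison is kept, label it exploratory and non-randomised.

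Cost: a little extra analysis, a wider interval and one added assumption to defend. Attendance must already be recorded for the present rule, and the sample size does not change.

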### Trial Objectives

To investigate whether people with PD and their spouses/carer who receive a programme of CAAT-PARK in addition to TAU show significantly greater rates of medication adherence and improved QoL from baseline to 12 week post randomisation compared to those who receive TAU only.

Secondary objectives are to investigate whether people who receive CAAT-PARK and those who receive TAU differ in terms of overall disease state, activities of daily living (ADL), beliefs about medication, generic health related QoL, and levels of carer distress. We will investigate whether baseline levels of cognitive impairment and anxiety and depression influence the effective uptake of CAAT-PARK. We also aim to investigate the experience of those receiving the intervention.

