### Inclusion Criteria

1. Adults diagnosed with, or with probable, Idiopathic PD (three out of four of the chief UK Brain Bank criteria).

2. Prescribed one or more anti-parkinsonian medications by a Consultant Neurologist or Consultant Physician with specialist knowledge of movement disorders.

3. English speaking and literate (participants are required to actively engage in the therapy process).

4. Stable medication regime i.e. not altered within the previous month and not expected to change during the period of the research project (12 weeks).

5. Not demented or significantly cognitively impaired. The clinical team will judge whether the patient has the cognitive capacity required to participate fully in the trial i.e. read patient information, complete self report questionnaires and engage actively in the therapy process.

6. Show poor adherence as determined by a MMAS-4 score ≥ 2.

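### The cognition and mood analysis is framed around impaired participants and merged with imbalance adjustment, so as written it does not test whether these factors change the treatment effect

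*Protocol article*

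**What the plan says.** The secondary objective, in the Trial Objectives section of the protocol article, reads: "We will investigate whether baseline levels of cognitive impairment and anxiety and depression influence the effective uptake of CAAT-PARK".

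The analysis meant to serve it is described in two places.

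- **Efficacy Analysis of Primary Outcomes:** the set is "participants with significantly high reported levels of cognitive impairment and anxiety and depression at baseline", as measured by MoCA and HADS, and these participants "will be analysed to determine the independent impact of these prognostic factors on the treatment effect". The sentence before it concerns adjustment for factors that are unevenly distributed between the arms. The sentence after it puts baseline imbalances into a regression model.
- **Prognostic Factors:** "Data collected for participants with identified cognitive impairment (assessed using the MoCA) or anxiety and depression (assessed using the HADS) will be appropriately adjusted", by regression. Then: "Where cognitive impairment and anxiety and depression are present in study participants at baseline assessment, analyses will be undertaken to assess their independent impact". The impact meant there is that on how well CAAT-PARK works.

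The carer question, in the same paragraph of the efficacy section, is worded differently: "All participants will undergo sub-group analysis testing for potential effect modification for the presence of a spouse/carer on the treatment effect".

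Inclusion criterion 5 requires participants to be "Not demented or significantly cognitively impaired", as judged by the clinical team. MoCA and HADS are completed by all participants before randomisation (Baseline Assessments).

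**The concern.** Whether a baseline factor changes a treatment effect is a question about a difference between effects. It needs participants across the range of the factor and a term that compares them. The text identifies the analysis by those who have the impairment and joins it to adjustment for chance imbalance, which is a different task.

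If an analyst follows the wording, the output will be a treatment effect in impaired participants, or an overall effect adjusted for MoCA and HADS, or both. Neither says whether cognition or mood alters the effect. The practical risk lies in interpretation. The Prognostic Factors section already anticipates that impairment may harm uptake of the intervention, and a non-significant result in a modest subset could be taken as confirming that.

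**Working it through.** **1. What each described analysis estimates.** Let D1 be the treatment effect in impaired participants and D0 the effect in unimpaired participants.

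| Analysis | Set | Quantity estimated |
|---|---|---|
| Needed for the objective | all randomised | D1 - D0, or the slope of the effect on the score |
| Analysis of participants with high levels | impaired | D1 |
| Regression on baseline imbalances | all randomised | one common effect, with D1 = D0 built into the model |
| Carer sub-group analysis | all randomised | the difference in effect by carer presence |

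Neither description of the cognition and mood analysis yields D1 - D0. Uptake in the objective could be taken to mean session attendance, but the two analysis sections refer to the treatment effect and to efficacy, so effect modification is the natural reading.

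**2. Inputs for an illustration.**

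- 40 per arm (80 in all), alpha 0.05, d = 0.69 on the PDQ-39 (6.13 / 8.89): Sample Size. Sidedness is not stated; two-sided is assumed.
- 20-30% with cognitive impairment: the figure in the Background section for people with Parkinson's disease. Using it for the trial sample is an assumption, as is an even split between arms.
- No prevalence is given for anxiety or depression, so 10% and 50% are added as a range.

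**3. The plan's own power figure.** Two-sample t-test, 40 per arm, d = 0.69, two-sided 0.05: power is 86%, against a stated 80%. The stated figure is on the cautious side and nothing below depends on it.

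**4. A test in the impaired participants alone.** Impaired per arm = 40 x prevalence; power is from the noncentral t distribution.

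| Prevalence | Per arm | Power for d = 0.69 | d detectable at 80% power |
|---|---|---|---|
| 10% | 4 | 13% | 2.38 |
| 20% | 8 | 25% | 1.51 |
| 30% | 12 | 37% | 1.20 |
| 50% | 20 | 57% | 0.91 |

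If the effect were d = 0.69 in everyone, so that there was no modification at all, the subset result would be non-significant in 63-75% of trials at 20-30% prevalence (100 - 37 and 100 - 25) and in 43% at 50%. A valid interaction test would wrongly signal modification in about 5%.

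**5. The replacement, on the same terms.** With a two-level modifier and SD units, the standard error of D1 - D0 is sqrt(2/n1 + 2/(40 - n1)), where n1 is the number impaired per arm. Power for a difference of 0.69 SD is Phi(0.69/SE - 1.96). The detectable difference at 80% power is (1.96 + 0.84) x SE.

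| Prevalence | n1 | SE | Power for 0.69 SD | Detectable difference |
|---|---|---|---|---|
| 20% | 8 | sqrt(0.250 + 0.0625) = 0.559 | 23% | 1.57 SD |
| 30% | 12 | sqrt(0.167 + 0.071) = 0.488 | 29% | 1.37 SD |
| 50% | 20 | sqrt(0.100 + 0.100) = 0.447 | 34% | 1.25 SD |

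With all 92 recruited and no attrition, the powers are 26%, 33% and 38%. These figures treat the modifier as two groups and take no credit for baseline adjustment.

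**The case against.** The strongest reply is that the wording is loose rather than restrictive. The text never says that the analysis is confined to impaired participants. An independent impact is regression language and makes little sense where everyone has the factor. The objective speaks of levels, and MoCA and HADS are collected from all. On that reading a regression in all participants was intended, and the model form and cut-offs belong in the analysis plan.

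Part of this stands. A reader might infer that unimpaired participants are expressly excluded, and the documents do not say that. Missing cut-offs and model formulae are not at issue here. But the charitable reading does not rescue the analysis, because the only regression described adjusts for imbalance, and that cannot answer the objective even when run in everyone. The impaired-participant framing also appears three times across two sections, while the carer question next to it has the right set and the right aim.

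Other stronger readings also fail:

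- **That the subset is bound to be very small.** This is plausible for cognition at the background prevalence. It is not shown for anxiety and depression, which the Medication Non-adherence section calls highly prevalent. Selecting non-adherent patients could also raise the share with impairment.
- **That criterion 5 removes most of the cognitively impaired.** It is a clinical judgement of capacity to take part, not a MoCA threshold, so milder impairment can remain.
- **That the plan will read non-significance as no effect.** It states no such rule; this is a risk of interpretation.
- **That low power argues for the replacement.** It does not, because the interaction test is imprecise too.

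**Conclusion.** The point holds as a mismatch between a stated method and its objective. As written, the cognition and mood analysis provides neither a contrast with unimpaired participants nor a test of effect modification, and it merges that question with covariate adjustment. This conclusion rests on the wording alone.

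The numbers are illustrative. They depend on an assumed 20-30% prevalence taken from background literature, an even split by arm, 80 analysed patients and two-sided 0.05. They show why significance or non-significance in the impaired participants should not be used to infer modification. They do not show that the trial could answer the question precisely under any wording: only differences in effect of about 1.25-1.57 SD would be detectable with 80% power at 20-50% prevalence.

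The matter is worth correcting but limited in reach. The objective is secondary, and the primary intention-to-treat comparison and the sample size are unaffected.

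**What to change.** Reword both sections as follows.

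- **Set and model:** in all randomised participants, for each primary outcome, regress the week-12 score on arm, its baseline score, the modifier and the arm-by-modifier term.
- **Modifiers:** MoCA and HADS, preferably as continuous scores, entered one at a time given about 80 patients. State whether HADS is used as a total or as its anxiety and depression parts. That gives 2 x 2 = 4 interaction estimates with the total, or 3 x 2 = 6 with the parts.
- **Reporting:** interaction estimates with 95% confidence intervals, labelled exploratory. State that modification will not be inferred from significance or non-significance in the impaired participants.
- **Separation:** describe covariate adjustment for prognostic factors or imbalance in its own sentence, applied to all participants, and drop the wording about adjusting the data of impaired participants.

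The cost is a change of wording. The data are already collected from everyone before randomisation. The downside to state openly is that the interaction estimates will have wide intervals, so an inconclusive result is likely.

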### Description of Primary Measures

#### Morisky Medication Adherence Scale (MMAS-4)

The MMAS-4 is a self-report scale for identifying medication non-adherence [35] and has been used in PD [16,41]. The scale is constructed of four items answered by 'yes' or 'no'. Four 'no' responses signifies perfect adherence. Any 'yes' responses indicates some degree of non-adherence with medication. We aim to recruit people scoring two or more 'yes' responses.

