### Sample Size

We will recruit a total of ninety-two family units (patient/carer pairs or patients alone), 46 per treatment group. This includes an additional 15% (n = 6) for potential participant attrition in each group. Where possible we aim to recruit patients with a spouse/carer, however, we will not exclude patient participants who do not have a spouse/carer but are wishing to participate. Using the primary outcomes, a pragmatic sample size of 40 participants per treatment group would provide an alpha of 0.05 and an 81% power to detect a difference of 25% improvement in medication adherence in the intervention group (detected by a one point shift in the MMAS-4) against 0% in the control group. This also provides 80% power to detect a Cohen's effect size of 0.69 in the PDQ-39, based on the published standard deviation of 8.89 in this patient group [43]. This would allow a difference in means of 6.13 (8.89 × 0.69) units in the PDQ-39.

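### A normality check decides whether each primary outcome keeps its t-test of mean change, so the primary test and effect measure depend on the observed data

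*Protocol article*

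**What the plan says.** Under Efficacy Analysis of Primary Outcomes, the protocol article determines efficacy by "comparing the mean change in values of the two groups from baseline to week 12 follow-up". The test is given as "Analysis between the two groups will be made using an independent sample" t-test.

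The same section then states the switch: "If normal distribution assumptions are not met, even after suitable transformations, non-parametric analysis will be adopted". Nothing limits it to one outcome, so it applies to MMAS-4 and PDQ-39 alike.

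Missing data follow directly: "Imputation for missing/incomplete data will be carried out using chained equations with all outcome measures and potentially correlated baseline values". The number of imputations is fixed: "A total of 10 imputed datasets will be created".

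Two other places determine what MMAS-4 change can look like. The description of the scale says "The scale is constructed of four items answered by 'yes' or 'no", and the sixth inclusion criterion is "Show poor adherence as determined by a MMAS-4 score ≥ 2". The Sample Size section rests on "a pragmatic sample size of 40 participants per treatment group". It states the PDQ-39 target as a difference in means of 6.13 units and the MMAS-4 target as 25% improving against 0%.

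**The concern.** The section names a mean difference as the measure of efficacy and then orders its replacement if the data look non-normal. This is a stated rule, so a statistical analysis plan could not drop it without contradicting the protocol.

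For MMAS-4 the trigger can be foreseen: a score with so few possible values is not normal, and no transformation makes it continuous. For PDQ-39 the trigger cannot be predicted from the document. The trial could therefore report a mean difference for one primary outcome and something else for the other.

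At stake is whether the result can be read against the plan: an estimate in scale points with an interval, combined over the imputed datasets and set beside the planned difference and the regression-adjusted estimates promised in the same section.

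**Working it through.** **1. The plan's own target.** 0.69 × 8.89 = 6.134, which reproduces the stated 6.13. It is a difference in means. With 40 per group, the normal-approximation power is Φ(0.69 × √(40/2) − z) = Φ(3.086 − z):
- two-sided 0.05: Φ(3.086 − 1.960) = 87.0% (exact t: 86.2%)
- two-sided 0.025: Φ(3.086 − 2.241) = 80.1% (exact t: 78.7%)

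The stated 80% matches 0.025 rather than the stated 0.05. That does not affect this point, so both levels are carried below.

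**2. Range of MMAS-4 change.** Baseline is 2, 3 or 4 and week 12 is 0 to 4. Change runs from 0 − 4 = −4 to 4 − 2 = +2, at most seven values. A one-to-one transformation of seven values still has seven values.

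**3. How often a check would fail.** The documents give no MMAS-4 distribution, so these are assumptions. Baseline shares at 2/3/4 were 50/35/15%, 34/33/33% or 60/30/10%. Week-12 scores came from a binomial on four items, from baseline problems persisting with a set probability, or from small steps around baseline. There were 40 per arm and tests were at 5%. Samples held about 4 to 6 distinct change values on average.

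| Check | Trials rejecting normality |
|---|---|
| Shapiro-Wilk, at least one arm | 99.6-100% |
| Shapiro-Wilk, pooled residuals (no effect) | 84-100% |
| Lilliefors, at least one arm | 100% |
| Shapiro-Wilk after log(change + 5), at least one arm | 100% |
| D'Agostino skewness/kurtosis, at least one arm | 6-36% |

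A separate simulation (baseline 55/32/13%, rounded and clipped scores) gave 98.4% for Shapiro-Wilk on residuals with no effect and 93.1% with a shift of 0.6.

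**4. Type I error for MMAS-4 change, nominal 5%.**

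| Rule | Main scenarios | Separate simulation |
|---|---|---|
| t-test | 4.7-5.1% | 4.8% |
| Mann-Whitney | 4.6-5.1% | 4.8% |
| Two-stage switch | 4.6-5.1% | 4.8% |
| Better of the two tests | not run | 5.5% |

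**5. Power.** For MMAS-4, t-test against Mann-Whitney gave 58.2 v 56.9%, 30.8 v 29.5%, 83.3 v 81.9% and 76.3 v 75.9% in the four effect scenarios, and 70.6 v 69.5% in the separate simulation. The rank test loses 0.4 to 1.4 points.

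For PDQ-39, if change were normal, the rank test acts like a t-test on 40 × 3/π = 38.2 per group. Power is Φ(0.69 × √(38.2/2) − 1.960) = 85.4% against 87.0%, or 78.1% against 80.1% at 0.025.

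**6. Agreement and effect measure.** The two tests disagreed on significance in 1.4-1.6% of trials with no effect and 2.7-5.6% of trials with one. With a true effect, the arm medians were equal in 21-59% of trials, so a report by medians could show no difference where the means differ.

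**7. Pooling.** With 10 imputations, Rubin's rules average the estimates and take total variance as W + (1 + 1/10)B, where W is the within-imputation and B the between-imputation variance. Each dataset must supply an estimate and a variance. A mean difference does; a rank-test p-value or a raw median comparison does not do so directly. The imputed datasets could also disagree on whether normality holds.

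**The case against.** The strongest reply is that no inferential harm has been shown. Type I error stays at about 5% and power moves by about one point. This stands: a reader might infer that letting the data choose the test inflates false positives, and the calculations do not support that. Even taking the better of the two tests gave only 5.5%.

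Three further objections also narrow the point.

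- **The check is not named.** A reader might infer that the t-test will almost never be used for adherence. That holds for Shapiro-Wilk or Lilliefors, but a skewness/kurtosis test usually passed and a visual judgement might too. For PDQ-39 there is no evidence either way.
- **Non-parametric need not mean a rank test.** A bootstrap or permutation analysis of the mean difference would fit the sentence and keep the effect measure. The choice of fallback, the normality criterion and the transformations may properly be left to the statistical analysis plan, so their absence is not the fault here.
- **Imputation is not ruled out.** A reader might infer that the fallback and the imputation are incompatible. They are not: a normalised rank statistic, or a shift estimate with a standard error, can be pooled. Only the direct route is lost.

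Nor is the MMAS-4 planning target a mean difference that the switch would lose: it is a proportion defined by a one-point shift. The lost comparison is clearest for the 6.13 units on PDQ-39.

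None of this removes the rule itself.

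**Conclusion.** The point holds in a limited form. The protocol sets a mean-change comparison as primary and then requires a data-dependent replacement for either primary outcome. For MMAS-4 the replacement is likely under a formal test of normality such as Shapiro-Wilk (84-100%) and uncertain under other checks. If the replacement is a rank test, the pre-specified estimate, its interval and direct pooling over the 10 datasets are given up in exchange for no gain in error control at 40 per group. The percentages rest on assumed MMAS-4 distributions. The range of −4 to +2 and the wording of the rule do not. The change is worth making because it is cheap and settles the primary effect measure, not because the planned tests would mislead.

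**What to change.** Delete the switching sentence. For each primary outcome, fix in advance one analysis of the mean difference at week 12: a linear model adjusted for the baseline score, with robust or bootstrap standard errors, pooled by Rubin's rules over the 10 imputed datasets and reported whatever a normality check shows. Add a rank-based or ordinal analysis, named in advance, as a sensitivity analysis.

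Removing the switch is what cures the defect. The baseline adjustment is an improvement that needs no new data, since baseline MMAS-4 and PDQ-39 are collected before randomisation and the section already plans a regression on pre and post scores.

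The cost is one changed sentence and one extra sensitivity analysis.
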